### Interventions

Participants in all conditions attend the workshop, receive the CPT manual and related materials, and have access to resources available through the free CPT-web online training (https://cpt.musc.edu/index). All participants who upload the required number of session recordings and patient symptom measures will be eligible to receive ‘CPT Provider’ status. This status is not tied to any change in remuneration for services. Provider status will be awarded to clinicians who demonstrate an acceptable level of fidelity to CPT based on session recordings randomly selected from the last two weeks of the six-month post-workshop period. Workshop participants who provide informed consent are randomized to one of the three post-workshop consultation conditions after completing the workshop. Participants in the two tele-consultation conditions receive six months of weekly one-hour group tele-consultation with a CPT expert. Each call includes discussions of the CPT protocol, challenging cases, treatment obstacles, and specific issues raised by participants within each group. Both tele-consultation conditions include a maximum of six to eight clinicians per call. CPT experts provide consultation across both consultation conditions to control for any expert-related effects. The prescribed and proscribed activities for each consultation condition are described in manuals, and study team members ([name], [name], ML) review consultant calls on a monthly basis to ensure that fidelity to the consultation condition is maintained. Consultants are trained by study team members prior to beginning consultation calls and receive consultation and feedback every four to six weeks or as needed for the first two waves of consultation, and as needed during the third consultation wave.

### Inclusion and exclusion criteria

Mental health clinicians from the Operational Stress Injury clinics, Canadian Forces mental health services, and the broader Canadian community are eligible to participate in the study if they: attend a CPT workshop; are licensed as a mental health clinician and are able to practice independently; currently provide psychotherapy to patients with PTSD; consent to be randomized to one of the study conditions; and are willing to solicit patient participation. Eligible patient participants are: diagnosed with PTSD; and consent to have their sessions audio-recorded and listened to by a fidelity rater and potentially other clinicians teaching and learning CPT. Patients are permitted to continue other psychotherapeutic interventions if they are not specifically focused on treating PTSD symptoms. Ineligible patients include those not eligible for CPT based on the state of research evidence, including those with: current uncontrolled psychotic or bipolar disorder; substance dependence; imminent suicidality or homicidality that requires acute care; and significant cognitive impairment (although mild to moderate traumatic brain injury is permitted).

### Outcome measures and assessment procedures

#### Fidelity ratings and assessment of CPT modification from audio-recorded CPT sessions

This study uses a modified version of the CPT fidelity measure [54] that has been used in previous clinical trials [55]. The CPT fidelity measure examines clinicians’ adherence to, and competence in, delivering specific CPT interventions prescribed in each session. Clinicians are rated on their adherence and competence in delivering these elements (rated on a 7-point, Likert-type scale). Two studies have assessed the reliability of the measure and found 97% agreement between two raters across all items for adherence in one study (agreement was not reported for competence scores; [55]) and 100% agreement for adherence and overall competence ratings in another [56]. Pilot research has been conducted to assess the predictive validity of the unique and essential scales for a small sample of veterans. CPT competence was highly correlated across all sessions with competence in cognitive therapy as measured by a validated cognitive therapy fidelity-assessment instrument, r = 0.82, p = 0.001 [44,57]. Therapist competence in the first session of CPT was positively correlated with self-reported symptom improvement among patients from baseline to post-treatment, r = 0.79, p = 0.02. Additionally, we use a framework of modifications to identify any deviations from or adaptations to CPT that occur in the sessions [58]. At least 10% of the sessions will be rated by all raters to independently assess inter-rater agreement.

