**Methods:**

The current study investigates whether clinicians receiving post-workshop support (six-month duration) will deliver CPT with greater fidelity (*i.e*., psychotherapy adherence and competence) and have improved patient outcomes compared with clinicians receiving no formal post-workshop support. The study conditions are: technology-enhanced group tele-consultation; standard group tele-consultation; and fidelity assessment with no consultation. The primary outcome is independent assessment (via audio-recordings) of the clinicians’ adherence and competence in delivering CPT. The secondary outcome is observed changes in patient symptoms during and following treatment as a function of clinician fidelity. Post-consultation interviews with clinicians will help identify facilitators and barriers to psychotherapy skill acquisition. The study results will inform how best to implement and transfer evidence-based psychotherapy (*e.g*., CPT) to clinical settings to attain comparable outcomes to those observed in research settings.

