### Research questions and hypotheses

Question 1: The principal research question to be addressed is whether different types of post-workshop support for mental health clinicians have differential effects on clinician fidelity to the CPT protocol.

Hypothesis 1: We hypothesize that the technology-enhanced group tele-consultation condition will evidence the highest levels of fidelity, the standard group tele-consultation condition will evidence intermediate levels of fidelity, and the no consultation condition will evidence the lowest fidelity.

Question 2: Is clinician fidelity to the CPT protocol is related to client outcomes?

Hypothesis 2: We hypothesize that fidelity to the CPT protocol, irrespective of consultation condition, will be positively associated with improved client outcomes.

Question 3: What are contextual barriers or facilitators to the skilled use of CPT in their routine practice?

Hypothesis 3: We hypothesize that organizational contextual variables such as local leadership support, organizational structure, and organizational climate, as well as clinician attitudes toward EBPs will influence the uptake of CPT.

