### Clinician demographic characteristics and experience

A pre-workshop questionnaire is administered to assess relevant clinician demographic information (*i.e*., age, gender, education), clinician experience (years of licensed practice, hours of formal training in CBT, hours of supervised post-graduate CBT training), prior CPT training experience (workshop hours and supervision hours), experience treating clients with PTSD (number of clients), and volume of current clinical activity (caseload and hours devoted to psychotherapy).

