### Proposed analytic strategy

Trial reporting will follow the CONSORT 2010 statement for reporting randomized controlled trials [69]. Analyses will be preceded by careful examination of the descriptive statistics and distributional form of all variables. The effectiveness of randomization will be evaluated by comparing the different conditions on baseline measures, demographics, and key outcome variables using Chi-squared tests and t-tests. The primary analyses will be conducted using random effects regression modeling. These models provide more flexibility in modeling missing data than general linear models and are appropriate for nested data. ‘Intention-to-train’ principles will be used in the analyses of clinicians who are assigned to a consultation modality but either fail to engage or are unable to fulfill the post-workshop participation requirements (*e.g*., do not attend consultation sessions). Analyses of both the intention-to-train and completer samples will be conducted.

To explore the contribution of organization and clinician-level factors to the outcomes of interest, in addition to random effects regression modeling, we will conduct qualitative analyses on interview data. Qualitative and quantitative data will be integrated to facilitate a fine-grained understanding of processes and characteristics that influence training outcomes. Interviews will be analyzed in line with goals, objectives and key research questions. Using content analysis, we will identify analytical categories to describe and explain our observations. Our work will occur in five stages outlined in Pope, Ziebland, and Mays’ framework approach to qualitative analysis [70]: Familiarization; Identifying a Thematic Framework; Indexing; Charting; and Mapping and Interpretation. In the second stage, codes will be derived deductively by identifying categories at the beginning of the research (*e.g*., elements of the CFIR), and inductively by identifying those that emerge gradually from the data. In subsequent phases, survey data on contextual factors will be examined in conjunction with fidelity scores for the purposes of validation, hypothesis generation, and expansion [71,72] to understand ways in which contextual factors influence fidelity to CPT.

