Although fidelity is a key implementation outcome in the model by Proctor and colleagues [73] and in this study, fidelity to EBPs has not been adequately assessed by independent evaluators in prior implementation research. It has either not been assessed at all, or has been assessed through self-report, standardized patient protocols [74], or a single session selected by providers (c.f., [52,75]). Our third innovation is to improve upon this methodological limitation of prior studies by randomly selecting audio-recorded sessions for fidelity monitoring. We will also conduct the only investigation of the effect of clinician fidelity to an EBP in routine care settings on PTSD outcomes to date. Because this investigation will examine sessions from novice clinicians who received varying intensities of consultation, we expect to see a greater range of fidelity than that seen in previous investigations of the impact of fidelity on symptom outcomes, as most studies to date have used clinical trial data with sessions from closely supervised clinicians. Finally, no evidence-based guidance exists regarding how to facilitate fidelity to the CPT protocol and ultimately patient outcomes. Using transcripts from consultation sessions, members of our research team will develop and test a theory of evidence-based consultation.

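### Hypothesis 2 is a non-randomised comparison open to confounding by clinicians' general therapy skill, yet the Discussion calls its result an effect and the article ties no clinician covariate to it

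*Protocol article*

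**What the plan says.** Under Research questions and hypotheses, the protocol article predicts that "fidelity to the CPT protocol, irrespective of consultation condition, will be positively associated with improved client outcomes". The Abstract defines the secondary outcome in the same terms: "observed changes in patient symptoms during and following treatment as a function of clinician fidelity". Both are statements of association. The Discussion goes further and presents the study as "the only investigation of the effect of clinician fidelity to an EBP in routine care settings on PTSD outcomes to date".

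The section on fidelity ratings gives two pilot results for the measure, in a small sample whose size is not stated. The first is that "CPT competence was highly correlated across all sessions with competence in cognitive therapy", with r = 0.82 and p = 0.001. The second is that first-session competence correlated with symptom improvement, with r = 0.79 and p = 0.02.

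The section on clinician characteristics collects, before the workshop, "clinician experience (years of licensed practice, hours of formal training in CBT, hours of supervised post-graduate CBT training". It also collects prior CPT workshop and supervision hours, and the number of PTSD clients treated.

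The Proposed analytic strategy uses baseline measures to compare the randomised conditions. It refers to clinician-level factors in a sentence that begins "To explore the contribution of organization and clinician-level factors to the outcomes of interest". It names random effects regression as the model and states no covariate for Hypothesis 2.

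**The concern.** The trial's argument has two links: consultation raises CPT fidelity, and fidelity improves patients. Randomisation protects the first link only. For the second, a clinician who is a better therapist in general may score higher on CPT fidelity and also have patients who improve more for reasons outside the CPT protocol.

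Neither of two common adjustments removes this. A term for consultation condition does not, because skill varies between clinicians within each arm. Patient baseline severity does not, because skill belongs to the clinician.

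If the association came from general skill, Hypothesis 2 would still be reported as supported, and the Discussion's wording would present it as an effect of fidelity. A reader could then conclude that raising CPT fidelity through consultation will help patients, which the slope alone cannot establish. The article collects data that would reduce the problem but does not assign them to this model.

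**Working it through.** **Step 1: what the pilot correlation can bear.** The inputs are r = 0.82 and p = 0.001, from the fidelity ratings section. The n is not given, so it is recovered from t = r·√[(n − 2)/(1 − r²)].
- n = 11: t = 4.30, p = 0.0020.
- n = 12: t = 4.53, p = 0.0011.
- n = 13: t = 4.75, p = 0.0006.

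The reported p fits n of about 12. The Fisher interval is tanh(1.157 ± 1.96/√9) = tanh(1.157 ± 0.653), or 0.46 to 0.95. Shared variance is 0.82² = 0.67 at the point estimate, with a range of about 22% to 90%.

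**Step 2: how much confounding could produce.** Inputs from the article:
- 90 clinicians (30 per condition).
- Four rated sessions each, with within-provider correlation 0.38.
- Two patients each, the required minimum.
- Correlation 0.82 between clinician fidelity and general skill, which borrows a competence figure for fidelity as a whole.

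Assumptions not in the documents:
- Fidelity has no effect once general skill is given.
- General skill explains a share v of patient outcome variance.
- The covariates capture a share R² of general skill.
- The agency effect is ignored, and clinician means stand in for the random-intercept model.

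Calculation for v = 0.05:
- Reliability of a four-session mean: 4 × 0.38/(1 + 3 × 0.38) = 1.52/2.14 = 0.710.
- Correlation of rated fidelity with skill: 0.82 × √0.710 = 0.691.
- Correlation of the two-patient mean outcome with skill: √[0.05/(0.05 + 0.95/2)] = √(0.05/0.525) = 0.309.
- Spurious fidelity–outcome correlation: 0.691 × 0.309 = 0.213.
- Chance of a significantly positive slope: Φ(atanh(0.213) × √87 − 1.96) = Φ(2.02 − 1.96) = 0.52, against a nominal 0.025.

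**Step 3: what adjustment removes.** The partial correlation given the covariates is 0.213 × (1 − R²)/√[(1 − 0.691²R²)(1 − 0.309²R²)], tested with √86 in place of √87.
- R² = 0.25: partial r = 0.173, Φ(1.616 − 1.96) = 0.365.
- R² = 0.50: partial r = 0.125, Φ(1.168 − 1.96) = 0.21.

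A simulation of the same set-up (6,000 replicates per cell) gave 53%, 36% and 22% for v = 0.05.

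**Step 4: sensitivity (simulation).**

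| Share of outcome variance, v | Unadjusted | R² = 0.25 | R² = 0.50 | R² = 0.75 |
|---|---|---|---|---|
| 3% | 35% | 24% | 15% | 8% |
| 5% | 53% | 36% | 22% | 10% |
| 8% | 73% | 54% | 32% | 13% |

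At the lower pilot limit (r = 0.46) the unadjusted rates over the same v are 14% to 29%. At the upper limit (0.95) they are 44% to 85%. If the covariates capture only a tenth of skill, the rate at v = 5% falls only from about 52% to about 46%.

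**The case against.** The case on the other side has four parts.

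First, Hypothesis 2 is worded as an association, and a covariate list is commonly left to an analysis plan that is not shown. That stands as far as the missing list goes. It does not cover the Discussion, which calls the slope an effect in the text as written.

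Second, a reader might infer from r = 0.82 that CPT competence is mostly general skill that clinicians brought with them. The article does not support that. The implied sample is about 12 and the interval is wide. The Background describes CPT as itself a cognitive therapy, so agreement with a cognitive-therapy scale is what convergent validity would look like. Both scores measure competence, with no measure of skill before training, and adherence is not covered. General skill alone would also need a correlation of 0.79/0.82 = 0.96 with outcome to produce the pilot's 0.79. That is implausible at the point estimates, although the intervals are too wide to exclude it.

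Third, a reader might infer that clinician variables are kept out of the outcome models. The Proposed analytic strategy can be read as planning regression on clinician-level factors, with qualitative work added. That also stands. The stated purpose is exploratory, however, and nothing links it to the Hypothesis 2 slope.

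Fourth, years and hours are imperfect proxies, and some may be poor choices. Prior CPT training may act on patients mainly through CPT fidelity, so adjusting for it could remove variation that Hypothesis 2 is meant to study. This is correct, and it limits both the covariate set and what adjustment can promise.

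**Conclusion.** The point holds in a limited form. Hypothesis 2 is an observational comparison pooled over arms, general therapy skill is a credible common cause, and the Discussion's causal wording goes beyond the design. The pilot figure is compatible with such confounding but does not demonstrate it.

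The size cannot be fixed from the documents. With no true fidelity effect and general skill explaining 5% of outcome variance, false support occurs in about 52% of trials unadjusted, 36% if covariates capture a quarter of skill and 21% if they capture half. The 5% and the capture shares are assumptions. Adjusting for the collected data would therefore reduce the bias; a reader should not infer that it removes it.

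No sample size or power figure changes, and the randomised Hypothesis 1 comparison is unaffected.

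**What to change.** 1. In the random effects model for Hypothesis 2, add as fixed covariates the pre-workshop years of licensed practice, hours of CBT training, hours of supervised CBT and number of PTSD clients treated. Report the adjusted slope beside the unadjusted one.
2. Add prior CPT workshop and supervision hours in a sensitivity analysis only.
3. In the Discussion, replace effect with association, and state that residual confounding by general therapy skill remains after adjustment.

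The cost is a short addition to the analysis text, a few degrees of freedom out of about 90 clinicians, and probably a slightly wider interval for the fidelity slope. No new data are needed.

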### Patient outcome measures

Patients are asked to complete measures related to their PTSD symptoms, functional impairment and overall quality of life at baseline (pre-treatment), at every alternate CPT treatment session, and at post-treatment follow-up (three months post-treatment). The assessment measures include: ‘The Posttraumatic Stress Disorder Checklist’ (PCL-S; [59]), a 17-item questionnaire that reliably measures the severity of distress related to PTSD symptoms (Chronbach’s alpha = 0.94). Each item is measured on a 5-point Likert scale, which maps on to the DSM-IV criteria for PTSD; ‘The Outcome Questionnaire – 45’ (OQ- 45; [60]), a 45-item self-report measure of three dimensions of client functioning in the past week: symptom distress (*e.g.*, anxiety, depression), interpersonal problems, and social role adjustment (Chronbach’s alpha = 0.71 to 0.93). The OQ-45 has established clinical cut-offs and a reliable change indices to signal meaningful improvements or deterioration; and ‘The Short-Form Quality of Life Health Survey’ (SF-12; [61]), a 12-item survey that measures mental components (vitality, social functioning, role-emotional, and mental health) and physical components (physical functioning, role-physical, bodily pain, and general health) of health related to quality of life. All questionnaires are available in English and French, and take clients around 15 to 20 minutes to complete. Therapists upload summary scores to a secure website at the same time that they upload their audio-recordings.

### Clinician demographic characteristics and experience

A pre-workshop questionnaire is administered to assess relevant clinician demographic information (*i.e*., age, gender, education), clinician experience (years of licensed practice, hours of formal training in CBT, hours of supervised post-graduate CBT training), prior CPT training experience (workshop hours and supervision hours), experience treating clients with PTSD (number of clients), and volume of current clinical activity (caseload and hours devoted to psychotherapy).

### Clinician monthly CPT activity reporting

During the six-month active study period, all clinicians complete a monthly report via a web-based survey on CPT activity. Questions include: the number of CPT sessions provided over the past month (irrespective of patients’ enrollment in the study); cumulative number of new CPT clients seen; frequency, duration, and satisfaction with consultation over the past month (as applicable); and a rating of clinician confidence in their ability to adhere to adherence to the CPT protocol.

### Quantitative and qualitative measurement of potential barriers and facilitators to CPT skills uptake and implementation outcomes

The Organizational Readiness to Change Questionnaire [62] is a pre-workshop self-report questionnaire that assesses various elements of a clinician’s perceived support for training implementation. A total of 18 scales (Chronbach alphas = 0.56 to 0.92) are grouped within four dimensions of readiness (*i.e*., motivation for change, adequacy of resources, staff attributes, organizational climate). The Dimensions of Organizational Readiness-Revised (DOOR-R; [63]) scale assesses perspectives on intra- and extra-organizational implementation readiness. The Evidence-Based Practice Attitudes-50 (EBPAS-50; [64]) is a 50-item, self-report measure of clinician attitudes toward EBPs, consisting of 12 factors, with moderate to large factor loadings and fair to excellent internal consistency reliabilities.

We also interview clinicians at baseline, post-consultation, and three months post-consultation to further assess for barriers and facilitators to the use of CPT in their practice. The interviews query effective tactics and methods that may have been used outside of the consultation methods (*i.e*., positive deviance; [65]) that the clinicians deemed helpful in acquiring and maintaining CPT skills. We based our interview questions on those used to assess influences on training and implementation in previous research [66], which are based in part on the Consolidated Framework for Implementation Research (CFIR [67]).

### Sample size and justification for power calculations

In conducting power calculations, we considered assessment attrition, within-clinician correlation, and within-setting effects. Based on a power curve calculation with the following assumptions: 30 clinicians per condition; 4 sessions rated for fidelity per clinician, randomly selected over time; with an alpha-level of 0.05, within provider correlation estimated at 0.38, 10% proportion of variance accounted for by the random effect associated with agency, based on a two-sided test, the detectable effect size for at least 80% power will be medium to large, per Cohen’s [68] classifications, ranging from d = 0.41 to 0.55.

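### The power calculation omits correlation within tele-consultation groups, so the stated detectable effect is too favourable, most of all for technology-enhanced versus standard consultation

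*Protocol article*

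**What the plan says.** The section on sample size and power names what was taken into account: "In conducting power calculations, we considered assessment attrition, within-clinician correlation, and within-setting effects". The assumed design is "30 clinicians per condition; 4 sessions rated for fidelity per clinician, randomly selected over time". The test is two-sided, and the other inputs are "alpha-level of 0.05, within provider correlation estimated at 0.38, 10% proportion of variance accounted for by the random effect associated with agency". The result is a detectable d of 0.41 to 0.55 at 80% power or more. The section does not say which contrast each end of the range refers to, or what attrition rate was used.

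Under Interventions, clinicians are randomized individually after the workshop. Those in the two tele-consultation arms then join a one-hour group call every week for six months: "Both tele-consultation conditions include a maximum of six to eight clinicians per call". On consultants, the section says "CPT experts provide consultation across both consultation conditions to control for any expert-related effects". The third arm has fidelity monitoring only and no groups.

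The Background section describes learning from other members' recorded sessions as part of how the technology-enhanced strategy is meant to work.

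The analytic strategy says "The primary analyses will be conducted using random effects regression modeling" and adds that such models suit nested data. It does not name the levels.

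**The concern.** Clinicians who share a call share discussion, case material and feedback for six months, so their fidelity scores can be expected to resemble one another more than those of clinicians in different calls. The power basis has terms for clinician and agency. Agency is the workplace and does not stand in for the call group. A calculation without a group term treats the 30 clinicians in a tele-consultation arm as independent once agency is allowed for, when they are taught in a handful of groups.

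The contrast most exposed is technology-enhanced versus standard consultation, because both of its arms are grouped. Hypothesis 1 predicts a difference there, between the highest and the intermediate level of fidelity. If the detectable effect is really larger than stated, a null result on that contrast is less informative than the protocol suggests.

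**Working it through.** **Inputs from the protocol article.** Sample size section: 30 clinicians per condition, 4 rated sessions each, within-clinician correlation 0.38, agency 10% of variance, two-sided alpha 0.05, 80% power. Interventions: at most six to eight clinicians per call, in two arms only.

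**Assumptions.** ρ is the share of single-rating variance due to consultation group, taken as 0.01 to 0.05. m is the actual group size, taken as 5 to 8. Eight is the upper limit in the text. Five follows if the three waves were equal: about 10 clinicians per arm per wave, split into two calls.

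**Step 1: the stated figure.** With rating variance set to 1, the variance of a clinician's mean over 4 sessions is v = (1 + 3 × 0.38)/4 = 0.535. For 30 versus 30, detectable d = (1.960 + 0.842) × √(2 × 0.535/30) = 0.529. Power at d = 0.55 is 83%.

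- Upper end: adding agency as 10% of the remaining variance raises the correlation to 0.38 + 0.10 × 0.62 = 0.442. Then v = (1 + 3 × 0.442)/4 = 0.5815 and d = 0.552, close to 0.55.
- Lower end: 0.41 was approached only by comparing 30 with 60 (the two consultation arms pooled) and removing the agency variance, v = 0.535 − 0.10 = 0.435. Then d = 2.802 × √(0.435 × (1/30 + 1/60)) = 0.413. For 30 versus 30, power at d = 0.41 is 58% with v = 0.535 and 67% with v = 0.435.

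No single variant gives both ends, so the exact calculation was not reproduced. Neither match uses a group term.

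**Step 2: add the group term.** In a grouped arm, the variance per clinician for the arm mean becomes v + (m − 1)ρ. In the control arm it stays at v.

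- Technology-enhanced versus standard: d = 2.802 × √(2[v + (m − 1)ρ]/30)
- Consultation versus none: d = 2.802 × √([2v + (m − 1)ρ]/30)

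| ρ | m | v + (m − 1)ρ | d, enhanced v standard | Power at 0.55 | d, consultation v none | Power at 0.55 |
|---|---|---|---|---|---|---|
| 0 | any | 0.535 | 0.53 | 83% | 0.53 | 83% |
| 0.01 | 5 | 0.575 | 0.55 | 80% | 0.54 | 82% |
| 0.01 | 8 | 0.605 | 0.56 | 78% | 0.55 | 81% |
| 0.02 | 5 | 0.615 | 0.57 | 78% | 0.55 | 80% |
| 0.02 | 8 | 0.675 | 0.59 | 74% | 0.56 | 78% |
| 0.05 | 5 | 0.735 | 0.62 | 70% | 0.58 | 76% |
| 0.05 | 8 | 0.885 | 0.68 | 62% | 0.61 | 72% |

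These are normal approximations. With few groups per arm, small-sample degrees of freedom cost more. At ρ = 0.05 and groups of 6 to 8, a t test on group-level degrees of freedom (about 5.5 to 8) has 46-56% power at d = 0.55 for technology-enhanced versus standard.

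**Step 3: break-even.** Power at d = 0.55 is 80% when v + (m − 1)ρ = 15 × 0.55²/2.802² = 0.578. From v = 0.535 the slack is 0.043. It is used up at ρ = 0.043/4 = 0.011 for groups of 5 and 0.043/7 = 0.006 for groups of 8. With v = 0.5815, the variant that matches the stated upper end, there is no slack. With v = 0.435, the break-even for groups of 6 to 8 is about 0.02-0.03.

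**Step 4: if the fitted model left group out.** The true error of a nominal 5% test is about 2Φ(−1.96/√DE), where DE is the ratio of true to assumed variance.

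- Technology-enhanced versus standard: DE runs from 0.615/0.535 = 1.15 to 0.885/0.535 = 1.65, so type I error is about 7% to 13%.
- Consultation versus none: DE runs from (0.535 + 0.615)/1.07 = 1.07 to (0.535 + 0.885)/1.07 = 1.33, so about 6% to 9%.

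These figures take the whole share as arising from the group itself. Simulation (40,000 trials per cell, experts assumed balanced across the two arms) gives about 4-5% for the first contrast if the whole 2-5% share comes from the expert, and about 6-8.5% if half does.

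**The case against.** The strongest reply is that the article condenses a fuller plan. It promises random effects regression for nested data, and an analysis plan that is not shown may include consultation group. That stands. A reader might infer that the primary standard errors will be too small, but the text neither includes nor excludes a group term, so Step 4 is conditional. The two consequences are also largely alternatives: modelling group costs power, and ignoring it inflates type I error.

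A second reply is that experts work in both consultation arms. A reader might say that this controls nothing unless expert is in the model. That goes too far. If the crossing is balanced, expert main effects cancel from technology-enhanced versus standard, and leaving the term out makes that test slightly conservative. What crossing does not remove is correlation from shared peers and case material, and it does not help consultation versus none.

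Third, the text does not say that group membership is fixed or that one expert leads each group throughout, and six to eight is a maximum. Treating each arm as four or five units is therefore an inference, which is why groups of 5 are included above.

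Fourth, no group correlation is given, and at 1% the loss is slight. That limits the size of the point, not its direction. None of these replies supplies a group term for the power calculation, whose result is stated in the article on a listed basis.

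**Conclusion.** The point holds for the power basis. The stated range of d = 0.41 to 0.55 leaves out a source of correlation that the design creates in two of three arms, and it is too favourable for any positive group correlation. With a group share of 2-5% and groups of 5 to 8, power at d = 0.55 for technology-enhanced versus standard falls from 83% to 62-78%, and for consultation versus none to 72-80%. These figures rest on an assumed correlation and on a base calculation that comes near the stated range without fully reproducing it.

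It would go too far to conclude that 80% power is shown to be lost. At a 1% share, power at d = 0.55 stays at 78-80% for the more exposed contrast. Inflated type I error is likewise not documented and depends on how the model is specified.

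**What to change.** Restate the detectable effect as a partially nested design over a declared range of group correlation, for example 0.01-0.05, using the actual number and size of groups, and say which contrast each figure refers to. Name in the primary model a random intercept for consultation group in the two tele-consultation arms only, with each control clinician as a unit of one, alongside the clinician and agency terms and with small-sample degrees of freedom (Satterthwaite or Kenward-Roger). A fixed expert effect is not needed, and it would be undefined for controls, who have no expert.

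The cost is a few lines of text, a less favourable detectable effect and wider intervals. Recruitment had passed its goal and the third consultation wave was under way when the article was written, so the sample size does not change and no extra data are needed. The benefit is a model fixed before analysis and a fair reading of a null result between the two consultation arms.
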